### Concomitant Care

The investigators monitored the participants for any concomitant treatment they received during the study period. In the event of any AEs, the use of rescue medication was permitted under the investigator’s discretion. All instances of concomitant care were carefully documented in the CRF. However, any study participant prescribed a conventional medication for a longer duration (more than 6 consecutive days) during the study period must discontinue use of the Ayush intervention during that period. This threshold distinguishes brief, incidental, or rescue medication use from sustained therapy that could potentially interact with or confound the effects of the study intervention. All such instances were documented in the CRF. If any participant developed a serious AE or a treatment-emergent AE during the study period, the participant was withdrawn from the study and given appropriate incidental care at the hospital. The government authorities and the Ethics Committee were notified within 2 working days, along with an appropriate justification.

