### Compliance With the Study Interventions

All participants in the AG group were provided with an information leaflet containing instructions for the use (dose, frequency, and time of administration) and storage of the Ayur-nutri kit. The participants were also issued a compliance form during the baseline visit and subsequent follow-up visits to self-report their consistent or irregular use of Ayush interventions in the Ayur-nutri kit and to record any missed doses, along with remarks for missing doses, which enabled the assessment of adherence to the dosing pattern as per the study protocol. During each follow-up visit, the participants were asked to return the used, unused, or partially used sachets of the Ayur-nutri kit to the investigators to assess adherence and cross-check with the participant’s self-reported compliance form. The participants were advised to maintain an open communication channel with the research team to address any issues they faced, including missed doses, adverse effects, and general health-related queries.

Adherence to the 60-minute daily yoga protocol was systematically monitored through instructor-maintained attendance logs at each site and also from the participant’s compliance diary. Daily session attendance was recorded for every participant throughout the intervention period.

The participants who did not adhere to the study protocol, or did not have 80% or more compliance, or those who developed any study-related AEs due to which the participant preferred to withdraw from the study, or those who withdrew their voluntary consent for participation in the study, were withdrawn from the study. If participants consented to data collection during the scheduled follow-ups or at the end of the 120 days, data were collected and recorded in the case report form (CRF). The data from completed assessments, available until the withdrawal, were used for analysis.

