### Outcome Measures

The primary outcome was the incidence of AMS, assessed using the 2018 Lake Louise Scoring System (LLSS). AMS is defined as an LLSS score of 3 or more points from the 4 rated symptoms (headache, nausea or vomiting, fatigue, and dizziness or light-headedness), including at least 1 point from headache [9]. The grading of LLSS score is mild AMS 3‐5 points, moderate AMS 6‐9 points, and severe AMS 10‐12 points [9]. The participants were assessed daily for the first 7 days at the stage I high-altitude areas using the LLSS score to record the incidence and evaluate the severity of AMS. The primary outcome will be reported as the proportion of participants who display symptoms of AMS and the proportion of participants with a score of more than 6 as per the LLSS. The participants enrolled for stage II were again assessed daily during their first 4 days at that altitude for the incidence and severity of AMS.

The secondary outcome measures included the proportion of participants who developed thromboembolic events (deep-vein thrombosis, pulmonary embolism, cerebral venous thrombosis, myocardial infarction, etc) during the study, change in the levels of markers of coagulation and hemostasis activation (total red blood cell count, hemoglobin, packed cell volume, D-dimer, lactate dehydrogenase, creatine kinase, creatine kinase-myocardial band, fibrinogen, activated partial thromboplastin time, prothrombin time), changes in the levels of proinflammatory markers (high sensitivity C-reactive protein, interleukin-6, tumor necrosis factor-α); self-reported changes in negative emotional states of depression, anxiety, and stress assessed through Depression Anxiety Stress Scale-21 item (DASS-21); change in sleep quality assessed through the Pittsburgh Sleep Quality Index (PSQI), and quality of life assessed through the 12-item short-form (SF-12) questionnaire. The secondary outcomes were evaluated on day 60 and day 120 from baseline. However, the participants enrolled for the stage II high-altitude area were also assessed on day 10 (day 4 of the AS at that altitude) and on the day of descent, in case of early descent before day 120.

Resting heart rate, systolic and diastolic blood pressure, respiratory rate, and oxygen saturation (SpO2) were also documented daily until day 7, alongside LLSS at stage I high altitude, and until day 10 in participants at stage II high altitude. These measurements were then taken on scheduled follow-up visits.

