### Sample Size

Based on the findings from a previous study on similar conditions, the anticipated incidence of AMS within the CG was 25%, while the assumed incidence in the AG was 18% [7]. To achieve a statistical power of 90% and a CI of 95%, an initial sample size of 722 per group was calculated. Accounting for an expected attrition rate of 15%, the final sample size for each group was determined to be 830 participants (N=1660 in total). The sample size of 1660 participants was stratified into stage I high altitude and stage II high altitude. A total of 830 participants were included from stage II high altitude, while the remaining 830 were from stage I high altitude. The participants studied at each of the 2 altitude stages were randomly allocated to the AG and CG.

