### Data Collection

The baseline demographics, clinical, and physical examination aspects were collected by qualified Ayush study personnel and reported in a CRF designed for this purpose. Subjective and objective outcome assessments were conducted according to the protocol (Table 3).

**Table 3. T3:** Study schedule.

	Screening	Baseline	Day 1 to 7	Day 10 (for participants at stage II HA^a^)	Day 30	Day 60	In case of early descent	Day 120
Written informed consent	✓							
Eligibility evaluation	✓							
Demographics and medical history		✓						
Clinical assessment	✓	✓	✓	✓	✓	✓	✓	✓
Vital parameters (resting heart rate, systolic and diastolic blood pressure, respiratory rate, SpO_2_^b^)	✓	✓	✓	✓	✓	✓	✓	✓
CBC^c^	✓			✓		✓	✓	✓
LFT^d^, KFT^e^	✓					✓	✓	✓
HbA_1c_^f^ and ECG^g^	✓							
Lipid profile		✓				✓	✓	✓
LDH^h^, CK^i^, CK-MB^j^, fibrinogen, aPTT^k^, prothrombin time, hs-CRP^l^, IL-6^m^, TNF-α^n^		✓		✓		✓	✓	✓
Lake Louise Scoring System for AMS^o^ assessment		✓	✓	✓				
Assessment for thromboembolic events						✓	✓	✓
DASS-21^p^, PSQI^q^, SF-12^r^ questionnaire		✓		✓		✓	✓	✓
Rescue medication			✓	✓	✓	✓	✓	✓
Assessment of adverse events			✓	✓	✓	✓	✓	✓
Assessment of drug compliance			✓	✓	✓	✓	✓	✓

a HA: high altitude.

b SpO_2_: peripheral capillary oxygen saturation.

c CBC: complete blood count.

d LFT: liver function test.

e KFT: kidney function test.

f HbA_1c_: glycated hemoglobin.

g ECG: electrocardiogram.

h LDH: Lactate Dehydrogenase.

i CK: creatine kinase.

j MB: myocardial band.

k aPTT: Activated Partial Thromboplastin Time.

l hs-CRP: high-sensitivity C-reactive protein.

m IL-6: interleukin-6.

n TNF-α: tumor necrosis factor-alpha.

o AMS: acute mountain sickness.

p DASS-21: Depression Anxiety Stress Scale-21 items.

q PSQI: Pittsburgh Sleep Quality Index.

r SF-12: 12-item short-form.

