### Statistical Methods

The categorical data will be presented as numbers (percentages) and compared between groups using the *χ*^2^ test, while within-group comparisons will be performed by using the McNemar or Cochran Q-test. Continuous data following a normal distribution will be reported as mean (SD), and between-group comparisons will be performed using an independent sample *t*-test. Within-group comparisons for normal data will be performed using a paired sample *t*-test/repeated measures ANOVA. Nonnormal data will be reported as median (first quartile, third quartile), and between-group comparisons will be conducted using the Mann-Whitney test. Within-group comparison will be done using the Wilcoxon signed-rank test or Friedman test. Baseline variables, such as age, prior altitude exposure, and hydration-related indicators, will be examined descriptively and adjusted in multivariable models where relevant. Regression analysis will be performed to study the effect of confounding variables on the incidence of AMS. The data of participants having early descent will be analyzed with censored data models. A *P* value less than .05 will be considered significant. The SPSS version 28.0 is being used for statistical analysis.

The modified intention-to-treat analysis approach will be applied to handle missing data. The missing data for all participants for whom data are available for at least one visit post-baseline will be imputed. The last observation carried forward method will be used for imputing the missing values.

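### Follow-up recorded after study withdrawal appears to be left out of the analysis and replaced by last observation carried forward

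*Protocol article*

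**What the plan says.** Four statements in the protocol article bear on this.

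- **Compliance With the Study Interventions** lists reasons for withdrawal from the study: non-adherence, compliance below 80%, a study-related adverse event (AE) after which the participant prefers to leave, and withdrawn consent. It then says: "If participants consented to data collection during the scheduled follow-ups or at the end of the 120 days, data were collected and recorded". The next sentence reads: "The data from completed assessments, available until the withdrawal, were used for analysis".
- **Concomitant Care** adds a further trigger: "If any participant developed a serious AE or a treatment-emergent AE during the study period, the participant was withdrawn from the study". No outcome event is exempted. Outcome Measures counts pulmonary embolism, myocardial infarction and cerebral venous thrombosis as secondary outcome events.
- **Statistical Methods** defines who is imputed: "The missing data for all participants for whom data are available for at least one visit post-baseline will be imputed". It also names the method: "The last observation carried forward method will be used for imputing the missing values". Participants who descend early are to be analysed with censored data models.
- **Data Collection, Table 3** schedules the coagulation and inflammatory markers, DASS-21, PSQI and SF-12 at baseline, day 60 and day 120. Day 10 is added for stage II only, and there is a further column for early descent. The blood count has screening as its only pre-treatment time. None of these measures is scheduled at day 30.

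**The concern.** Withdrawal from the study is treated as the end of usable data, even for participants who agreed to be followed and were followed. A value measured at day 60 or 120 would be set aside and an older value used in its place. For most of the secondary outcomes at stage I, that older value predates treatment, so the participant enters the analysis as unchanged.

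The comparison at stake is the between-arm difference in change at days 60 and 120. Withdrawal is unlikely to be equally frequent in the two arms. The Compliance section describes compliance forms, sachet returns and yoga attendance logs for the Ayush intervention, so the 80% rule falls mainly on that arm. Replacing recorded values more often in one arm moves the comparison by an amount unrelated to the treatment effect. Even when withdrawal is balanced, it distorts the estimate for the participants as randomised. The article gives no reason for preferring a carried-forward value to a measured one.

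**Working it through.** The plan gives no figure for this point, so the first step is to follow the rules through. The arithmetic after that shows scale only.

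**1. A stage I participant withdrawn at day 30 for compliance below 80%, who consents to later visits.**

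- Compliance is assessed at day 30 (Table 3), so withdrawal before day 60 can occur.
- The daily Lake Louise visits in days 1 to 7 give at least one post-baseline visit, so the participant is in the imputed set.
- Day 60 and day 120 biomarkers and questionnaires are measured and entered in the case report form.
- These fall after withdrawal, so on the plain reading they are not analysed and count as missing.
- LOCF looks back. Table 3 has no post-baseline value of these measures before day 60 at stage I, so baseline (screening for the blood count) is carried forward and the change is 0.

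A stage II participant withdrawn after day 10 would have the day 10 value carried forward instead. Anyone withdrawn between days 60 and 120 would have the day 60 value carried to day 120.

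**2. The same participant, withdrawn for a serious thromboembolic event.** The event itself has been observed. What is lost is the later follow-up. The steps are the same if the Compliance section's data rule covers Concomitant Care withdrawals. If the participant descends early, Table 3 provides an assessment at descent, and the censored-data rule may apply instead. The article does not say which rule takes precedence.

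**3. Size of the error.** Let w be the share of an arm withdrawn before day 60 whose later value was recorded but not used, and d the true mean change in those participants, in SD units. The arm mean is off by −w × d, so the Ayush-minus-control difference is off by

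−(w_Ayush × d_Ayush − w_control × d_control).

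With the same d in both arms this is −(w_Ayush − w_control) × d. Its sign depends on which arm loses more participants and on whether the true change is improvement or worsening. The document gives none of these quantities.

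For stage I there are 830 / 2 = 415 per arm, so the standard error (SE) of a difference in mean change is sqrt(2/415) = 0.069 SD. Taking d = 0.5 to 1 SD as an assumption:

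| Assumed difference in w between arms | Error in the difference (SD) | In SE |
|---|---|---|
| 0 | 0 | 0 |
| 1.8 points | 0.009 to 0.018 | 0.13 to 0.26 |
| 5 points | 0.025 to 0.05 | 0.36 to 0.72 |
| 15 points | 0.075 to 0.15 | 1.08 to 2.16 |

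The 1.8-point row is what would follow if one in ten of the assumed 18% AMS cases in the Ayush arm, and none among controls, were withdrawn in this way (0.18 × 0.10 = 0.018). The 15-point row borrows the attrition rate in Sample Size and puts all of it in one arm, before day 60, with every participant consenting to later data. It is an outer illustration and not an expectation.

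If withdrawal is balanced and the true difference is the same in withdrawn participants as in the rest, the estimate shrinks by the factor 1 − w. At w = 15% that is 0.85 of the true difference.

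**4. Serious thromboembolic events alone.** No rate is given. If 0.1% to 1% of participants had one, 1660 × 0.001 = 1.7 to 1660 × 0.01 = 16.6, so about 2 to 17 participants are affected.

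**The case against.** The strongest reply is that the Compliance section does not say that only data up to withdrawal are used. One can read the two sentences together as meaning that consenting participants continue to supply data, and that for everyone else whatever exists up to withdrawal is kept. That is possible, but it is not what the second sentence says. It draws no line between those who consented and those who did not, and no other section brings post-withdrawal data into the analysis.

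Two further objections stand in part. The consent and data-use sentences follow the Compliance section's own list of reasons, which does not name the serious or treatment-emergent AE rule in Concomitant Care. Extending them to that rule is a reasonable inference, since the wording is general and the list already includes study-related AEs, but it remains an inference. Also, a participant taken to hospital for a serious event may descend early and be analysed with the censored-data models instead.

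Three stronger readings should not be drawn.

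- **That AMS cases are themselves withdrawn, so the primary outcome is compromised.** The article does not say AMS was handled as an AE. Table 3 has separate rows for the Lake Louise score, for "Assessment for thromboembolic events" and for adverse events. Concomitant Care ties withdrawal to hospital care and notification. An AMS case is in any event scored before it could lead to withdrawal.
- **That stage I Lake Louise scores are carried into stage II.** The article says: "The participants enrolled for stage II were again assessed daily during their first 4 days at that altitude". It states no rule that fills those days from stage I, and whether LOCF crosses the two windows is detail that an analysis plan would settle.
- **That the error favours the Ayush arm.** The sign depends on quantities the document does not give.

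**Conclusion.** The concern holds in a limited form. As written, recorded day 60 and day 120 values of withdrawn participants are set aside and earlier values used instead. At stage I, withdrawal before day 60 generally means a recorded change of zero. This is a rule the article states, not a detail it omits. It applies directly to withdrawals in the Compliance section and by inference to those in Concomitant Care, except where the early-descent rule takes over.

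Neither size nor direction can be computed from the document. On the assumptions shown, the error is well under one standard error unless withdrawal is frequent and markedly unequal between arms. AMS incidence is largely unaffected. The exposed outcomes are mainly secondary, and the article's limitations section calls the study exploratory for these. The case for acting is that the Results section describes the analysis as still in progress and the measured values, where they exist, are already on file.

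**What to change.** State in the analysis wording, before results by arm are examined, that:

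1. Participants are analysed as randomised, using all data recorded after a kit halt or a study withdrawal.
2. LOCF, if kept, is used only where no value was recorded.
3. Stage II Lake Louise days are not filled from stage I scores. This is a clarification, since the article is silent on it.
4. Withdrawals are reported by arm, stage and reason, with the number who have later values recorded. This count gives w in each arm and shows how much the rule matters.

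It would help to add one sentence on whether the early-descent rule or the withdrawal rule takes precedence when both apply.

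The cost is a short change of wording and one count from existing case report forms. No new data are needed and clinical care does not change. There are three drawbacks. Data recorded off the intervention dilute the estimated effect slightly. Participants who did not agree to further collection remain missing. Coagulation markers measured after treatment for a thromboembolic event reflect that treatment, so a sensitivity analysis excluding those values could be reported alongside.

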### Outcome Measures

The primary outcome was the incidence of AMS, assessed using the 2018 Lake Louise Scoring System (LLSS). AMS is defined as an LLSS score of 3 or more points from the 4 rated symptoms (headache, nausea or vomiting, fatigue, and dizziness or light-headedness), including at least 1 point from headache [9]. The grading of LLSS score is mild AMS 3‐5 points, moderate AMS 6‐9 points, and severe AMS 10‐12 points [9]. The participants were assessed daily for the first 7 days at the stage I high-altitude areas using the LLSS score to record the incidence and evaluate the severity of AMS. The primary outcome will be reported as the proportion of participants who display symptoms of AMS and the proportion of participants with a score of more than 6 as per the LLSS. The participants enrolled for stage II were again assessed daily during their first 4 days at that altitude for the incidence and severity of AMS.

The secondary outcome measures included the proportion of participants who developed thromboembolic events (deep-vein thrombosis, pulmonary embolism, cerebral venous thrombosis, myocardial infarction, etc) during the study, change in the levels of markers of coagulation and hemostasis activation (total red blood cell count, hemoglobin, packed cell volume, D-dimer, lactate dehydrogenase, creatine kinase, creatine kinase-myocardial band, fibrinogen, activated partial thromboplastin time, prothrombin time), changes in the levels of proinflammatory markers (high sensitivity C-reactive protein, interleukin-6, tumor necrosis factor-α); self-reported changes in negative emotional states of depression, anxiety, and stress assessed through Depression Anxiety Stress Scale-21 item (DASS-21); change in sleep quality assessed through the Pittsburgh Sleep Quality Index (PSQI), and quality of life assessed through the 12-item short-form (SF-12) questionnaire. The secondary outcomes were evaluated on day 60 and day 120 from baseline. However, the participants enrolled for the stage II high-altitude area were also assessed on day 10 (day 4 of the AS at that altitude) and on the day of descent, in case of early descent before day 120.

Resting heart rate, systolic and diastolic blood pressure, respiratory rate, and oxygen saturation (SpO2) were also documented daily until day 7, alongside LLSS at stage I high altitude, and until day 10 in participants at stage II high altitude. These measurements were then taken on scheduled follow-up visits.

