**Methods:**

The proposed open-label, parallel-group RCT was conducted in apparently healthy individuals of any gender aged 18‐50 years. The study was conducted at two distinct high-altitude stages within the western Himalayan region: stage I, situated at an elevation ranging from 9000 to 12,000 feet and stage II, spanning 12,000 to 15,000 feet. A total of 1660 participants (n=830 per stage) underwent random assignment in a 1:1 ratio to receive either the existing acclimatization schedule (AS) for high altitude (control group) or the Ayush intervention (Ayush group) in addition to the AS. The participants in the Ayush group received Ayurvedic nutritional supplements, including the Ayur-nutri kit (Ayush poshak yoga, 25 g, and Ayush cardiac care tea, 125 mL), twice daily, along with a yoga protocol (60 min daily) for 120 days. The primary outcome was the incidence of AMS, assessed using the 2018 Lake Louise Scoring System, and the proportion of participants with a Lake Louise Scoring System score of 6 or higher during the first 7 days from baseline. The secondary outcome measures included the proportion of participants with thromboembolic events; changes in coagulation and hemostasis activation markers and proinflammatory markers; and changes in self-reported negative emotional states (depression, anxiety, and stress), sleep quality, and overall quality of life (assessed through Depression Anxiety Stress Scale-21 items, Pittsburgh Sleep Quality Index, and 12-item short-form, respectively) on day 60 and day 120 from baseline.

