### Strengths and Limitations

The present RCT protocol has particular key strengths. First, the use of nutritional supplements enriched with Ayurveda herbs, which are easy to use, palatable, and safe, with the potential to address AMS and related conditions. Second, the study has a large sample size, validated subjective assessment tools, and biomarkers to address various circulation and hemostasis-related parameters. This protocol also has a few limitations, including the open-label design of the study. However, to remove any potential bias, the research staff assigned to assess the study outcomes will be unaware of the allocation of participants to the study groups. Furthermore, there is an unequal attention between groups (due to oral interventions and supervised yoga routines in the AG) that may influence participants’ perceptions. Additionally, the altitude-exposure stage may influence the onset patterns of symptoms. Also, as the study is exploratory in nature for the secondary outcomes, it lacks power for multiple hypothesis testing across biomarkers, and no hierarchical testing plan or multiplicity adjustment was prespecified.

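### The severity part of the primary outcome has two incompatible cut-offs (6 or higher; more than 6), and its role beside AMS incidence is not fixed

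*Protocol article*

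**What the plan says.** **Cut-off.** The abstract's Methods paragraph gives the primary outcome as AMS incidence together with "the proportion of participants with a Lake Louise Scoring System score of 6 or higher during the first 7 days from baseline". The Outcome Measures section announces "the proportion of participants with a score of more than 6 as per the LLSS". In the same paragraph it sets out the grades: mild is 3 to 5 points, then "moderate AMS 6‐9 points", then severe at 10 to 12.

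**Role.** The Outcome Measures section opens in the singular: "The primary outcome was the incidence of AMS, assessed using the 2018 Lake Louise Scoring System (LLSS"). It then continues "The primary outcome will be reported as the proportion of participants who display symptoms of AMS" and adds the severity proportion in the same sentence. The Sample Size section uses AMS incidence only: 25% in the control group against 18% in the Ayush group, 90% power, 722 per group before attrition. The Statistical Methods section gives one general rule, that a P "value less than .05 will be considered significant", and compares categorical data by the χ² test. The Strengths and Limitations section says that no hierarchy or multiplicity adjustment was prespecified, but that sentence concerns a study that is "exploratory in nature for the secondary outcomes".

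**The concern.** A program that follows the abstract and one that follows the Outcome Measures section would produce different event counts for an outcome labelled primary. The article reports that data collection is complete and analysis is in progress, and the design is open-label. As long as both cut-offs stand in print, either result could be defended from the text.

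The second difficulty is what the severity proportion is for. It shares the primary label in the abstract and is reported under that label in the Outcome Measures section, but the trial was not sized for it. No sentence says whether incidence alone, either proportion or both must be significant. The false-positive rate for a primary claim depends on that answer.

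**Working it through.** **1. The two cut-offs side by side.** The grade bands (3–5, 6–9, 10–12) leave no gaps only if totals are whole points, so more than 6 means 7 or higher.

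| Score | Grade in Outcome Measures | Event under abstract | Event under Outcome Measures |
|---|---|---|---|
| 3–5 | mild | no | no |
| 6 | moderate | yes | **no** |
| 7–9 | moderate | yes | yes |
| 10–12 | severe | yes | yes |

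Only 6 or higher coincides with a grade boundary (moderate plus severe). The other wording splits the moderate grade. No assumption is needed for this step.

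**2. The plan's own sample size.** Inputs from the Sample Size section: p₁ = 0.25, p₂ = 0.18, power 90%, 95% confidence (taken as two-sided α = .05). With mean p̄ = 0.215,

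n = [1.960·√(2·0.215·0.785) + 1.282·√(0.25·0.75 + 0.18·0.82)]² / 0.07² = (1.139 + 0.742)² / 0.0049 ≈ 721.8, rounded up to **722** per group.

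This matches the stated figure exactly, so 722 is the number for AMS incidence tested alone at two-sided .05. The severity proportion does not enter it.

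**3. Error rate if either proportion could be claimed.** Let p be the AMS rate and q the severity rate, both under no treatment effect. If everyone counted for severity is also an AMS case, the two test statistics have correlation

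ρ = √[ q(1 − p) / (p(1 − q)) ].

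For p = 0.25 and q = 0.05, ρ = √(0.0375 / 0.2375) = 0.397. The family-wise error is 1 − P(|Z₁| < 1.96 and |Z₂| < 1.96) under the bivariate normal. The article gives no severity rate, so q is an assumption.

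| q (assumed) | p = 25% | p = 18% |
|---|---|---|
| 1% | 9.7% | 9.6% |
| 2% | 9.6% | 9.5% |
| 5% | 9.3% | 9.1% |
| 10% | 8.8% | 8.3% |
| 15% | 8.2% | 7.1% |

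Simulation of the χ² tests at 830 per group gives 9.8% (p = 25%, q = 2%), 9.2% (25%, 5%), 8.9% (25%, 10%) and 9.0% (21.5%, 5%). Independent tests would give 1 − 0.95² = 9.75%. The severity wording does not itself require a headache point. If some participants reach the cut-off without headache, nesting is incomplete and the result moves towards 9.75%.

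**4. Error rate under the other readings.** If incidence alone decides, it is 5%. If both proportions must be significant, it is at most 5%.

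**5. Cost of keeping two either-or primaries.** With a Bonferroni split (.025 each), 722 per group gives 84.1% power for 25% against 18%, and 90% power needs 853 per group before attrition.

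**6. Illustration only: what the cut-off could do to power for severity.** Suppose 5% of controls score 6 or higher and the intervention halves this. Power is then about 70% at 705 per group (830 × 0.85) and about 76% at 830. If 30% to 50% of those participants score exactly 6, the stricter cut-off leaves 3.5% against 1.75%, or 2.5% against 1.25%, with power at 705 per group of about 54% and 41%. None of these rates comes from the article.

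**The case against.** A reader might infer that the trial's primary false-positive rate is about 9%. The article does not support that. The figure needs a rule that success on either proportion is enough, and no such rule is stated. The Outcome Measures section names incidence in the singular, and the Sample Size section uses incidence alone. Both fit incidence as the deciding test with severity as support. The .05 threshold in Statistical Methods is a general convention and not a rule for declaring the trial positive. The admission about multiplicity concerns secondary outcomes. A decision rule is also something a statistical analysis plan would commonly hold, and that plan is not shown. All of this stands, and the error rate must be stated conditionally.

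It is also fair to say that the mismatch may be a slip in the article. A prospectively registered, ethics-approved protocol exists and may fix the cut-off, so one cannot assert that the choice will be made after seeing data. Nor can one infer that the trial is underpowered for severity: the rates in step 6 are invented for illustration, 705 applies the full 15% attrition to an outcome measured in the first days, and low power is no defect in a supportive outcome.

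The objection does not remove the contradiction in the cut-off, which is on the face of the text. It also leaves the abstract's wording, which puts both proportions under the primary label.

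**Conclusion.** The severity component is described in two incompatible ways, and the version in Outcome Measures conflicts with that section's own grading. That part is certain and rests on no assumption. Its effect on the event count is the number of participants whose score is exactly 6, which the article does not allow one to estimate.

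The role of the severity proportion is unclear. Under an either-or rule at .05 the family-wise error would be roughly 7% to 10%, conditional on the assumed severity rates and on (near) nesting; under an incidence-only rule it is 5%. The article does not establish which holds. The definition of AMS incidence (3 or more points with headache) and its 722 per group are not affected.

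**What to change.** - Write 6 or higher (moderate or severe AMS) wherever the severity proportion is defined, so that it agrees with the grading in Outcome Measures. Check this against the registered and ethics-approved protocol and record any difference.
- State that AMS incidence is the single primary outcome, the one for which 722 per group was computed.
- Call the proportion at 6 or higher a supportive or key secondary outcome, for example tested at two-sided .05 only if incidence is significant. Other arrangements would also do, such as a Bonferroni split with the power loss shown above, provided that one is named.
- Date and document these statements before any unblinded comparison, since analysis is reported to be under way.

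The wording changes are small, and incidence keeps its full .05 and planned power. The costs are the dated documentation and that severity could not be claimed on its own if incidence fails. Aligning the cut-off alone does not change the family-wise error, so the statement of roles is needed as well.
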